### Micro-level hypotheses

H1. Group singing may lead to increases in positive mood—more so than the participants in the control group.H2. Group singing may foster greater feelings of social closeness—more so than the participants in the control group.

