## Data analysis

### Statistical power analysis

An a priori power analysis was conducted to determine the sample size needed to detect the smallest effect size of interest. We determined the number of participants needed to detect the cross-level interaction of group (i.e., group singing vs. audiobook club) and time (i.e., *baseline* vs. *completion*) on SIN perception. The power analysis was conducted using traditional approaches where the resulting sample size refers to the level 2 clusters–in this case, the number of participants.

*G*Power* version 3.1.9.4 was used to conduct the analysis for an ANOVA within-between factor interaction [119]. For a conservative estimate, we assumed a small effect size of, η^2^ = .01, corresponding to an effect size of f = 0.1. We estimated the correlation among the repeated measures to be *r* = .62, based on a previous group-singing controlled trial that reported an intraclass correlation (ICC) of .62 [64]. Accounting for a 20% attrition rate [64], the power analysis (f = .10, *α* = .05, *r* = .62) suggests a total sample size of *N* = 206 participants, approximately *n* = 30 per site for 85% power.

In addition to the power analysis, we also calculated the reliability of our repeated measurements to assess for sufficient reliability for each participant based on [120] (1):

$$n_{min}=\frac{\rho (1-ICC)}{\left(1-\rho )(ICC\right)}$$
(1)

where *n* min is the number of time points and *ρ* is the population correlation across all the timepoints. Given our two timepoints and estimated ICC of .62, we have adequate-to-good reliability of our timepoints, *ρ* = .77.

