### Planned statistical analyses

#### Tests of equivalence

Given the sample size and random assignment to group, we assume that covariates such as age, gender, education, musical training/background, credibility, and expectation will be evenly distributed across the participants. Thus, we expect equivalence between participants and their randomly assigned intervention. To test this assumption, we will use a well-known technique to test for equivalence, the Bayesian *t*-test [121, 122]. Each Bayesian *t*-test will produce a coefficient called the Bayes Factor (BF), a measure of the likelihood of the alternative hypothesis (i.e., that the two samples differ). BF of 1 or less, will be interpreted as strong evidence for the null hypothesis [123]. Upon discovery of a BF larger than 1 we will conclude that the groups are not equivalent on this variable, and this variable will be used as a covariant in subsequently modeling of measures of interest.

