#### Difference score and outlier rejection

Outliers due to technical errors will be removed. Univariate outliers on continuous independent and dependent variables will be rejected based on a boxplot method, wherein a data point is an outlier if it falls 1.5 times outside of the interquartile range. Because each group may have unique distributions, we plan to reject outliers based for each group individually. For each of the micro-level dependent measures, a difference score will be computed (i.e., *pre-* to *post-session*).

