For each micro-level dependent variable, three separate MLMs will be defined: 1) an intercept-only model; 2) a main-effect only model (DV_change_ ~ *group + time*) and 3) an interaction (DV_change_ ~ *group * time*) model. For micro-level models, the time variable will reflect the time point of the micro-level observation and will allow us to model changes between the group across time. Similarly, three separate MLMs will be defined for macro-level dependent variables: 1) an intercept-only model; 2) a main-effect only model (DV ~ *group + session*) and 3) an interaction (DV ~ *group * session*) model. For both macro and micro-level models we will use a hierarchical modeling technique to determine which model is the best fit to the data. Model fit parameters will be compared between the three models and results of the model with the best fit will be reported on. Upon the discovery of a significant interaction, a follow-up simple slope analysis will be used to examine the differences in time (e.g., *baseline* vs. *completion*) across groups. For all hypothesis tests, alpha values will be set at 0.05.

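### A covariate added to correct imbalance cancels out of the macro group-by-session interaction, so the powered effect stays unadjusted for imbalance that affects change

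*Protocol article*

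**What the plan says.** Tests of equivalence (Data analysis, Planned statistical analyses) expects that "covariates such as age, gender, education, musical training/background, credibility, and expectation will be evenly distributed across the participants". Each variable is checked with a Bayesian t-test. If the Bayes factor exceeds 1, "this variable will be used as a covariant in subsequently modeling of measures of interest". The section does not say in what form the covariate enters, and no other remedy for imbalance is given.

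Modelling and inferential statistics prints the models. For macro outcomes the largest is "an interaction (DV ~ *group * session*) model", with a random intercept per participant. For micro outcomes the ladder includes "a main-effect only model (DV_change_ ~ *group + time" and the matching interaction model. Of the models fitted, "results of the model with the best fit will be reported on". None of the printed formulas contains a covariate, or a covariate crossed with session or time.

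Statistical power analysis sizes the trial to detect "the cross-level interaction of group (i.e., group singing vs. audiobook club) and time" on speech-in-noise perception, so the macro interaction carries the main test. The micro outcomes are already changes: "For each of the micro-level dependent measures, a difference score will be computed" (Difference score and outlier rejection).

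**The concern.** The covariates listed are handled as one value per participant. The macro treatment effect is a difference between arms in within-person change. A term that is constant within a person cannot explain change within that person unless it is crossed with session. Following the text as printed would therefore give a macro result described as adjusted for, say, unequal musical training, while the tested interaction is the unadjusted one. If musical training affects how much speech-in-noise scores improve between visits, that part of the difference would be credited to singing.

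Imbalance is not remote. Allocation is simple 1:1 randomisation within sites of about 30, and up to six or more variables are screened.

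**Working it through.** **1. The plan's own figure, to fix the target effect.** Inputs from Statistical power analysis: f = .10, alpha = .05, r = .62, 85% power, 20% attrition.
- Noncentrality for the within-between interaction with two visits: lambda = f² × N × 2 / (1 − r).
- N = 173 gives 0.01 × 173 × 2 / 0.38 = 9.1 and just over 85% power; N = 172 gives 84.9%.
- 172 × 1.2 = 206.4, which matches the stated 206.
- In a 2 × 2 interaction, f = .10 means cell deviations of ±0.10 SD, so the net difference in change is 4 × 0.10 = 0.40 SD.

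**2. The algebra.** Let person i in arm g have covariate c, random intercept u and visit t = 0 or 1:

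y = a + b·g + s·t + d·g·t + k·c + u + e

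Completion minus baseline is s + d·g + (e1 − e0). Both k·c and u have cancelled. With both visits observed, the estimate of d is the difference between arms in mean change, whether or not c is in the model. The planned random slope for group does not alter this, because group is also constant within a person. With covariate × session the change becomes s + d·g + m·c + (e1 − e0), and d is then adjusted for c.

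**3. Simulation of the macro model.** Settings: N = 206, r = .62, true interaction 0.20. Assumed, not from the protocol: imbalance 0.4 SD, covariate slope 0.5 on level and 0.3 on change. Mean interaction estimate over 30 data sets per row:

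| Data | No covariate | Covariate main effect | Covariate × session |
|---|---|---|---|
| Complete | 0.277 | 0.277 | 0.173 |
| About 20% covariate-dependent dropout | 0.327 | 0.336 | 0.213 |

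With complete data the first two columns differ by at most 2e-15. With dropout the estimate moves by 0.016 on average (maximum 0.041), but the bias is not removed. The last column agrees with 0.20 within simulation error.

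**4. Micro models.** Three occasions, complete data, 2,000 data sets, same imbalance, level slope 0.5, true group effect 0.20.
- Group × time: largest difference with and without the covariate 3e-15.
- Group main effect on the difference score: 0.399 without the covariate, 0.202 with it. Here the main-effect covariate does its job.

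**5. Size of the bias left in the macro test.** Assumptions: 105 per arm (half of 210), complete data, no true effect, imbalance 0.3 SD. An imbalance of 0.3 SD is about the smallest the Bayes-factor rule flags: for an assumed Cauchy prior scale of 0.5 to 1.0 the threshold is |t| = 1.88 to 2.15, and × sqrt(2/105) this is 0.26 to 0.30 SD.
- SE of the difference in change = sqrt(2 × 0.38) × sqrt(2/105) = 0.872 × 0.138 = 0.120.
- Bias = imbalance × slope of change on the covariate.

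| Slope (SD per SD) | Bias | Bias / SE | Two-sided rejection at .05 | Share of 0.40 SD |
|---|---|---|---|---|
| 0.1 | 0.3 × 0.1 = 0.03 | 0.25 | about 6% | 7.5% |
| 0.3 | 0.3 × 0.3 = 0.09 | 0.75 | about 12% | 22.5% |

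The 0.3 slope is a strong one. Against an SD of change of 0.87 it corresponds to a correlation of about one third between covariate and change.

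**The case against.** **The form is not stated.** The protocol article does not say that the covariate enters only as a main effect, and an analysis plan could settle it. This stands as a caution: the point rests on the natural reading of adding a covariate to the printed formulas. It does not dispose of the point, because the article fixes the trigger, the remedy and the model formulas, and taken together these leave the powered test unadjusted.

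**Adjustment does work elsewhere.** A reader might infer that the remedy for imbalance does nothing anywhere in the plan. The document does not support that. Micro outcomes are difference scores, and hypotheses such as "Group singing may lead to increases in positive mood—more so than the participants in the control group" are answered by the group main effect, which the covariate does adjust. The models of speech-perception difference scores under Mechanisms and contributions to speech perception would also be adjusted, if they count among the measures the covariate is meant for.

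**Data will not be complete.** The plan expects 20% attrition and rejects outliers, so exact invariance is not the case to be met in practice. True, but the estimate then shifts only slightly, and in the simulation not towards the truth.

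**The error rate is conditional.** A reader might take 12% as the trial's type I error. It is not. It applies only once a 0.3 SD imbalance has arisen and only at the steeper slope. For variables fixed before allocation, imbalance is chance, and the error rate over all randomisations stays at 5%.

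**Not every listed variable should be adjusted for.** Credibility and expectation are recorded in respect to the assigned group, so allocation may affect them. Crossing them with session would condition the treatment effect on a consequence of allocation. This stands, and it limits the fix.

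**Conclusion.** The point holds for the interaction terms, chiefly macro group × session. On the natural reading, a participant-level covariate added as a main effect leaves that estimate unchanged with complete data and nearly unchanged with dropout, so it does not correct imbalance that affects change. The cancellation is algebra and needs no assumed figure.

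The size does need assumptions. For a 0.3 SD imbalance, 105 per arm and r = .62, the bias left in place runs from about 0.03 SD to about 0.09 SD for slopes of 0.1 to 0.3 SD per SD, against a target of 0.40 SD. No passage supports a particular slope, so this is a range and not a prediction. The practical harm is that a macro result would be reported as adjusted when it was not.

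**What to change.** State the form in which covariates enter:
- **Macro models:** a baseline covariate used for adjustment enters with its interaction with session, DV ~ group * session + covariate * session. An alternative is to enter it in a model of the completion score adjusted for baseline. The two are not identical: the second estimates the slope on baseline, while the first in effect fixes it at 1 with complete data. One should be chosen in advance.
- **Micro models:** add covariate * time where group × time is interpreted. For the group main effect alone, the covariate main effect is enough.
- **Scope:** limit this to variables measured before allocation or unaffected by it. Handle credibility and expectation separately, for example as a sensitivity analysis.

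Cost: a sentence or two of analysis wording, one more fixed-effect parameter per covariate and no new data. At a 0.3 SD imbalance the standard error grows by a factor of about sqrt(1 + 0.3²/4) = 1.011, or roughly 1%, before any gain from a covariate that predicts change.

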#### Difference score and outlier rejection

Outliers due to technical errors will be removed. Univariate outliers on continuous independent and dependent variables will be rejected based on a boxplot method, wherein a data point is an outlier if it falls 1.5 times outside of the interquartile range. Because each group may have unique distributions, we plan to reject outliers based for each group individually. For each of the micro-level dependent measures, a difference score will be computed (i.e., *pre-* to *post-session*).

#### Modelling and inferential statistics

Due to the nature of this research design, there are various levels at which the data will likely show high levels of covariance (e.g., participant, group and site level), also known as clusters. Not accounting for this covariance can lead to inaccurate estimates of standard error, leading to inaccurate hypothesis testing (Mass & Cox, 2004). A well-known modeling technique that can account for this is mixed-effects linear modeling (MLM) and is also well suited to handle missing data in case of attrition or outliers (Pinheiro & Bates, 2000). MLM accounts for covariance at various levels using random effects, which allow for variance in the slope, or intercept. These random effects are defined within the model parameters based on the clustering in the research design. For our purposes, we will define a random-intercept for individual participant, to account for covariance in the repeated measures, and a random-slope for group, to account for the group level covariance.

The third level of nesting (i.e., site) is not accounted for in the model because we do not have hypotheses relating to the different sites. Modeling the third level will result in an unnecessary overly complicated model, but ignoring the third level of clustering could result in heteroscedasticity of model residuals, underestimated standard errors and biased *p*-values. To address this, we will plot and visually assess the proposed model’s residuals. If there is heteroscedasticity of the model residuals, we will apply a robust standard error estimator to account for the clustering [124]. All modeling will be done in the *lme4* package [125] in R.

For each micro-level dependent variable, three separate MLMs will be defined: 1) an intercept-only model; 2) a main-effect only model (DV_change_ ~ *group + time*) and 3) an interaction (DV_change_ ~ *group * time*) model. For micro-level models, the time variable will reflect the time point of the micro-level observation and will allow us to model changes between the group across time. Similarly, three separate MLMs will be defined for macro-level dependent variables: 1) an intercept-only model; 2) a main-effect only model (DV ~ *group + session*) and 3) an interaction (DV ~ *group * session*) model. For both macro and micro-level models we will use a hierarchical modeling technique to determine which model is the best fit to the data. Model fit parameters will be compared between the three models and results of the model with the best fit will be reported on. Upon the discovery of a significant interaction, a follow-up simple slope analysis will be used to examine the differences in time (e.g., *baseline* vs. *completion*) across groups. For all hypothesis tests, alpha values will be set at 0.05.

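### No planned model has a term for the choir or club, and the trigger for robust errors is insensitive to clustering, so standard errors will be too small if change is shared within choirs or clubs

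*Protocol article*

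**What the plan says.** Under Modelling and inferential statistics, the protocol article warns that "there are various levels at which the data will likely show high levels of covariance (e.g., participant, group and site level" and that ignoring this gives inaccurate standard errors. For the models themselves, the whole random part is an intercept for each participant "and a random-slope for group, to account for the group level covariance". Site is excluded: it "is not accounted for in the model because we do not have hypotheses relating to the different sites". The section concedes that leaving site out may understate standard errors, and offers a safeguard based on looking at the residuals: "If there is heteroscedasticity of the model residuals, we will apply a robust standard error estimator to account for the clustering".

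Under Statistical power analysis, the arms are defined as "group (i.e., group singing vs. audiobook club", and "the resulting sample size refers to the level 2 clusters–in this case, the number of participants". The sample size has no allowance for choirs, clubs or sites.

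The Participants section randomises individuals 1:1 within each of seven sites, 15 to each arm. The Training procedure section has each choir led by a choir master who adapts sessions to the group and settles repertoire with its members. Each audiobook club chooses its own books.

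**The concern.** Participants are randomised one by one but trained in groups that share a leader, material and one another. Members of one choir may therefore change together over the 12 weeks. The participant intercept absorbs stable differences between people and sites. It does not absorb change shared within a choir or club, and that change adds variance to the group-by-session effect (macro models) and to the group effect on the change score (micro models).

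The plan recognises the problem, but neither of its two safeguards addresses it. The random slope is attached to the participant, not to the choir or club. The robust-error step waits for unequal spread, whereas clustering is correlation. If shared change exists, p-values and confidence intervals for the arm comparison would be too optimistic. The psychosocial outcomes look most exposed, since closeness to the assigned group is itself measured.

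**Working it through.** **1. The plan's own figure.** Inputs from Statistical power analysis: f = 0.10, alpha 0.05, r = 0.62, two sessions, 85% power, 20% attrition.
- Noncentrality = f² × N × 2/(1 − r) = 0.01 × N × 2/0.38, with 1 and N − 2 degrees of freedom (df).
- N = 172 gives 84.9% power, and 172 × 1.2 = 206.4, which reproduces the stated 206.
- The target of 210 with 20% lost leaves 168 completers and 84.0% power, before any clustering.
- The implied effect on the change score is √(4 × 0.02/0.38) = 0.459 SD.

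**2. What the random slope can do.** Take group as arm (coded 0/1) and participant as the clustering unit.
- The between-person variance is σ₀² in one arm and σ₀² + 2σ₀₁ + σ₁² in the other. Three parameters rest on two estimable variances.
- The covariance between two different participants is zero whatever the slope variance.
- For 105 per arm with within-person variance 0.38, the standard error of group by session is √(2 × 0.38 × 2/105) = 0.1203. It stayed at 0.1203 for every slope variance tried.
- Macro model: 210 × 2 = 420 random effects against 210 × 2 = 420 observations. Fitted to simulated data of that size, lme4 stopped because the observations did not outnumber the random effects.
- Micro models: up to 210 × 3 = 630 records, so that count check passes, but the slope is still not separable from the intercept.

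**3. The trigger.** Formal heteroscedasticity tests on conditional residuals stood in for the visual check (3,000 runs). Share of trials flagged:

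| Check | ICC 0 | ICC 0.05 | ICC 0.20 |
|---|---|---|---|
| By session | 1.1% | 1.5% | 10.7% |
| Against fitted values | 11.9% | 10.5% | 11.3% |
| By arm | 8.2% | 9.8% | 14.4% |

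**4. Type I error of the planned test.** Assumptions not in the documents: one choir and one club per site (14 training groups), 12 completers in each (15 × 0.8), and the ICC of change. Let ρ be the total ICC and s the part shared by both arms of a site. The true variance of the arm contrast relative to the variance the model assumes is about k = 1 + 11ρ − 12s, and type I error is about 2 × [1 − Φ(1.96/√k)].

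| ρ | s | k | Formula | Simulation (8,000 runs) |
|---|---|---|---|---|
| 0 | 0 | 1.00 | 5.0% | 5.1% |
| 0.02 | 0 | 1.22 | 7.6% | 7.2% |
| 0.05 | 0 | 1.55 | 11.5% | 11.3% |
| 0.10 | 0 | 2.10 | 17.6% | 18.1% |
| 0.05 | 0.025 | 1.25 | 8.0% | 7.7% |
| 0.10 | 0.05 | 1.50 | 11.0% | 11.2% |
| 0.05 | 0.05 | 0.95 | 4.4% | 4.7% |
| 0.10 | 0.10 | 0.90 | 3.9% | 3.8% |

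With two training groups of 6 per site and arm and ρ = 0.05, none of it shared by the two arms, k = 1 + 5 × 0.05 = 1.25 and type I error is about 8%.

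**5. Power once clustering is respected.** Noncentral t with noncentrality 0.459/√(2k/84), s = 0. A comparison of the 14 training-group means has 12 df. With site as a fixed effect, 14 − 7 − 1 = 6 df remain.

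| ICC | 12 df | 6 df |
|---|---|---|
| 0 | 78% | 70% |
| 0.02 | 70% | 62% |
| 0.05 | 59% | 52% |
| 0.10 | 47% | 41% |

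**The case against.** Several points on the other side stand.
- **No ICC is given.** A reader might infer that standard errors will be too small in every model. The documents do not support that: the expectation of high covariance carries no value and is not about change scores. The outcome used for power, an adaptive speech-in-noise threshold measured in a booth, may show little shared change. At ICC 0 the planned test holds its level.
- **Site effects partly cancel.** A reader might infer that omitting site in itself makes standard errors too small. Randomisation is within site, so change common to both arms drops out of the contrast. If all the correlation is of that kind, type I error is at or below 5%. The harmful gap is at site-by-arm level.
- **The number of training groups is not stated.** Smaller groups would reduce the effect.
- **The trigger is not blind.** At ICC 0.20 some checks flag more often, so insensitive is the supportable word.
- **Group could be meant as a nesting level.** The section lists group among its clusters and calls site the third level, and no model formula is printed. A slope for arm across sites would be estimable and would pick up choir-level variation. But that reading needs site in the model, and the text excludes it. The macro fitting error would also be noticed rather than bias results silently.
- **The fall from 85% power is not all clustering.** Attrition from 210 brings it to 84%, and the loss of df alone takes it to 78% (12 df) or 70% (6 df) at ICC 0.

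None of this supplies a choir or club term or makes heteroscedasticity a suitable signal of correlation.

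**Conclusion.** The concern holds conditionally. As written, no model accounts for choir or club, the random slope cannot do what is claimed for it, and the robust-error step will usually not be called when it is needed. How far error control suffers depends on an ICC the documents do not give. With one choir and one club per site and 12 completers each, type I error runs from 5% to about 17.5% over site-by-arm ICCs of 0 to 0.10, and is lower where sites share the change or training groups are smaller. Confidence is high on the structure of the model and the trigger, and moderate on the size. It should be settled before the analysis, because the protocol itself names this correlation as a threat to its inference.

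**What to change.** Delete the random slope for group and the residual-plot trigger. In their place prespecify:
- **Macro models:** a participant intercept, site (fixed or random) acting on the completion session, and a random training-group effect (site by arm) on the completion session. A training-group intercept alone would not correct the group-by-session effect.
- **Micro models:** a participant intercept, site, and a random training-group effect, all on the change score.
- **Inference:** Kenward-Roger or Satterthwaite degrees of freedom. If a model does not converge, always use cluster-robust errors with a small-sample correction, clustering by site, within which choirs and clubs nest.
- **Power:** restate it over a range of ICC from 0 upward, starting from about 84% at 168 completers before clustering or loss of df.

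Site should not be left out of this repair. With all 14 training groups treated as unpaired at a total ICC of 0.05, simulated type I error falls to about 3% if half is shared by both arms and about 2% if all is. A comparison paired by site held 5% throughout.

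The change is to wording and code and requires no extra enrolment. The price is wider intervals, few degrees of freedom (as low as 6 with site fixed) and a lower stated power. Restoring 85% would take more training groups, which is a separate decision.

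### Reporting only the best-fitting of three models lets the effect the trial is powered on go unreported, and inflates it when it is reported

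*Protocol article*

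**What the plan says.** Under Modelling and inferential statistics, "three separate MLMs will be defined for macro-level dependent variables: 1) an intercept-only model", followed by a model with group and session as main effects, and "3) an interaction (DV ~ *group * session*) model". The decision rule is then: "Model fit parameters will be compared between the three models and results of the model with the best fit will be reported on". The same hierarchical comparison governs the micro outcomes, where the dependent variable is already a pre-to-post difference. A simple-slope follow-up is planned only after a significant interaction.

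Under Statistical power analysis, the target is the interaction: "We determined the number of participants needed to detect the cross-level interaction of group" and time on speech-in-noise perception. G*Power "was used to conduct the analysis for an ANOVA within-between factor interaction", with an effect "corresponding to an effect size of f = 0.1", r = .62, alpha .05, 85% power and 20% attrition, giving N = 206.

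Nothing in the protocol requires the interaction estimate to be shown when another model fits better.

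**The concern.** In this design the treatment effect on a macro outcome is the group-by-session term. The macro hypotheses are comparative (more improvement than in the control group), so they need that term. Two of the three candidate models do not contain it, and the data decide which model is reported. Three consequences follow.

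- The effect may not appear at all, most often when it is small or absent. Those are the results that a trial and later meta-analyses most need to see.
- If the main-effects model wins, the coefficient labelled group is the arm difference averaged over baseline and completion. It combines a chance baseline difference with half of the treatment effect.
- When the interaction is reported, it has passed a filter that favours large estimates, so it is biased away from zero.

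**Working it through.** **Inputs.** From the protocol: f = .10, r = .62, alpha .05, 20% attrition, N = 206 (210 recruited), 1:1 allocation. Completers: 210 × 0.8 = 168, or 84 per arm. Assumed here: complete pairs, equal variances, a participant random intercept, and a common session effect of either 0 or 0.2 SD (the protocol gives none).

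**The plan's own figure.** For a 2 × 2 within-between interaction, λ = f²·N·2/(1 − r) on 1 and N − 2 df. The exact f for η² = .01 is √(.01/.99) = 0.1005, which needs 172 completers for 85% power. 172 × 1.2 = 206.4, so N = 206 is reproduced. At 168 completers with f = .10, λ = .01 × 168 × 2/.38 = 8.84 and power is 84.0%.

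**Design effect in SD units.** The interaction shifts each cell mean by a quarter of the difference in change, so f = δ/4 and δ = 0.40 SD. Check: the variance of the difference in change is 2(1 − .62) × 2/84 = .0181, and .40²/.0181 = 8.84, the same λ.

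**Interaction against main-effects model.** The fit gain follows a noncentral chi-square with 1 df and λ = 8.84. The interaction model loses when the gain is below the criterion's threshold:

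| Criterion | Threshold | Loses at 0.40 SD | Loses at 0.20 SD (λ/4) | Loses at no effect |
|---|---|---|---|---|
| AIC | 2 | 5.9% | 46.9% | 84.3% |
| Likelihood ratio, .05 | 3.84 | 15.5% | 68.2% | 95.0% |
| BIC, ln(336 observations) | 5.82 | 28.7% | 82.2% | 98.4% |

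With BIC counted on 168 participants (threshold 5.12), the 0.40 SD figure is 23.9%.

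**All three models.** Simulation of 20,000 trials per scenario. For the likelihood ratio, interaction against main effects is tested first, then main effects against intercept-only. BIC counts observations. Ranges run over the two session effects.

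| Criterion | Interaction model not selected, truth 0.40 | Mean selected estimate, truth 0.40 | Mean selected estimate, truth 0.20 |
|---|---|---|---|
| AIC | 6–7% | 0.42 | 0.30–0.32 |
| Likelihood ratio | 15–16% | 0.44 | 0.35 |
| BIC | 29% (session 0.2 SD), 44% (none) | 0.46–0.48 | 0.40–0.45 |

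Repeat runs move the BIC figures by one or two points, to 31% and 45%. BIC depends on the session effect because, without one, the intercept-only model becomes a serious competitor.

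**Main-effects coefficient.** The expected arm difference is 0 at baseline and 0.40 at completion. The average is 0.20 SD (simulated 0.20).

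**Baseline adjustment.** Relative variance of the arm comparison:
- completion score alone: 1.00
- planned interaction, with complete data equal to the change score: 2(1 − .62) = .76
- baseline-adjusted: 1 − .62² = .6156

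The ratio of the last two is .6156/.76 = (1 + r)/2 = 0.81. At 168 completers λ becomes 8.84/.81 = 10.9 and power goes from 84.0% to 90.7%. The ratio is 0.75 at r = .5 and 0.90 at r = .8.

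**The case against.** The strongest reply is that comparing the main-effects and interaction models by likelihood ratio is itself the interaction test at .05. Model choice then only restates the test, and its type I error stays at 5%. That is correct and stands. It does not rescue estimation: a non-significant interaction still drops out of the report, and a significant one is still inflated. Naming the criterion could properly be left to an analysis plan, but none of the three criteria removes the problem. At the design effect the inflation is also modest under AIC or likelihood ratio (0.42 to 0.44 against 0.40); it is serious mainly for smaller effects or under BIC.

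Three stronger readings are tempting, and the document does not support them.

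- A reader might infer a false-positive rate of about 9%, through either a significant interaction or a significant group term. That requires a group main effect to count as benefit. No passage says so: the hypotheses are comparative, the power analysis targets the interaction, and follow-up is tied to a significant interaction.
- A reader might infer that the planned model is wrong or discards baseline. It does neither. `group * session` gives an unbiased difference in change under randomisation, matches the power calculation, and already captures most of the available gain (1.00 to .76, against .62). Adjustment is an improvement, not a correction.
- A reader might extend the half-effect argument to the micro outcomes. There the dependent variable is already a change score, so the main-effects group coefficient is itself a treatment contrast. Only the risk of non-reporting carries over.

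**Conclusion.** The concern holds for the reporting rule. Followed as written, it would leave the powered effect unreported in about 6% (AIC), 16% (likelihood ratio) or 30 to 45% (BIC) of trials in which the design effect is real, and far more often for smaller effects. It would also inflate the estimates that are reported, by up to about a fifth at 0.40 SD and by about one and a half to just over two times at 0.20 SD. These sizes assume 168 completers, complete pairs and r = .62; the BIC range also depends on an assumed session effect.

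The precision gain from baseline adjustment is real but secondary. It rests on an r that the protocol takes from one previous trial and gives only for speech-in-noise, so 84% to 91% should not be carried over to the questionnaires or the music tests.

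**What to change.** **Macro outcomes.** Replace the best-fit rule with one prespecified model per outcome. State that the between-group effect at completion will be reported with its 95% CI and p-value whatever the model fit, and keep the three-model comparison as description only.

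**Micro outcomes.** State that the group effect on change and the group-by-time test will always be reported, whichever model fits best.

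**Optional, at no cost in data.** Take the macro estimate from an ANCOVA of the completion score on group and baseline score. Alternatively, use a mixed model with equal baseline means: `DV ~ post + post:group` with a participant random intercept, where `post` is a numeric 0/1 completion indicator and there is no group main effect. The numeric coding matters: with `session` as a factor, `session + session:group` still has four mean parameters, including a baseline arm difference, and so is only `group * session` rewritten.

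**Cost.** A few sentences and one line of model code. No new data, visits or participants.
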